**Complications possibly related to feeding tubes:**
Complicated insertion (eg, nasal bleeding)Mechanical complications (feeding tube displacement and obstruction)
**Complications possibly related to parenteral feeding:**
Mechanical complications (occlusion and dislodging of central venous catheters)Clinical complications (pneumothorax, hemothorax, arterial puncture, and central line replacement because of the suspicion of catheter-related bloodstream infections)

Possible effects on nutritional intake and circadian rhythm.
**Nutritional intake**
The proportion of patients receiving at least a caloric intake of 67% of predicted resting energy expenditure (pREE) before or at the end of the first week and the proportion of patients receiving at least a caloric intake of 100% of pREE before or at the end of the first weekThe proportion of days caloric targets are reached divided by the total days in the study per patientMedian caloric intake as a percentage of pREEThe proportion of patients requiring supplemental parental nutrition beyond day 7The time to oral intake
**Circadian rhythm**
Cortisol and melatonin patterns in blood and in salivaCircadian rhythm in gene expressionSleep architecture (quantity and quality)Circadian rhythm in vital signs

Clinically relevant outcome measures.
**Clinically relevant outcome measures**
Time to final (live) weaning from mechanical respiratory support and duration of mechanical ventilationTime to final (live) weaning from pharmacological or mechanical hemodynamic support and duration of such supportTime to (live) discharge from the pediatric intensive care unit (PICU) and duration of PICU stayTime to (live) discharge from the hospital and duration of hospital stay for both the index hospitalization and total hospitalization, including stay in the referred hospitalNewly acquired infections, which are defined as a microbiologically or laboratory-confirmed infection in combination with the start of treatment or clinical suspicion of infection, as assessed by the clinician responsible for the patientMortality during the time window of the randomized intervention during PICU stay, during hospital stay, and after 30 daysAcute kidney failure: Patients in need of renal replacement therapy (RRT) during PICU stay and the duration of RRT (for patients requiring RRT); Patients with acute kidney injury according to the *Pediatric Risk, Injury, Failure, Loss, End Stage Renal Disease* criteria [35]Patients with newly acquired liver failure according to the *Pediatric Acute Liver Failure* criteria or with a clinical diagnosis of acute liver failure [36]

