## Methods

### Ethics Approval and Informed Consent Procedure

The protocol and informed consent forms were approved by the Dutch national ethical review board *Centrale Commissie Mensgebonden Onderzoek* (CCMO; NL72302.000.19). The monitor verifies that the trial will be performed in accordance with the protocol described in the European Medicine Agency’s *Note for guidance on good clinical practice CPMP/ICH/135/95* and the *Declaration of Helsinki*. Eligible patients and, if applicable, their parents or legal guardians, will be informed by one of the members of the research team orally in plain language and in writing. This member of the research team will not be involved in the treatment of the patient. Informed consent will be provided in writing by the parents or legal guardians and confirmed by the child if they are aged ≥12 years. Patients aged ≥16 years will be asked for consent if possible; otherwise, parents or legal guardians will act as legal representatives. For planned admissions, informed consent will be obtained before surgery if possible. For unplanned admissions (or patients with planned admissions whose consent could not be obtained before surgery), informed consent will be obtained within 24 hours after becoming eligible for the study.

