### Patients’ Eligibility

#### Inclusion Criteria

Upon admission to the PICU, all the children will be screened for eligibility for inclusion in the ContInNuPIC clinical study. All patients identified by the research team will be logged.

Critically ill children, term newborn to aged 18 years, who are likely to stay in the PICU for >48 hours and to be dependent on artificial nutrition, are eligible for inclusion.

Patients will be considered critically ill if they meet at least one of the following criteria:

Respiratory support (excluding low flow nasal cannula)Hemodynamic support (pharmacological or mechanical)Continuous renal replacement therapy on account of acute renal failure

Patients already on home respiratory support will be considered critically ill only if they have significantly deteriorated compared with normal functioning; that is, need for an increase in the level of support (eg, higher pressure rates, higher fraction of inspired oxygen, or need for hemodynamic support).

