### Data Collection at Study Entry

At baseline, data on demographic (age, sex, race, ethnicity, and preadmission body weight, and height) and clinical characteristics of the patients will be obtained. For all patients, risk of mortality scores (*Pediatric Index of Mortality score*) [16], disease severity scores (*Pediatric Logistic Organ Dysfunction score*) [17], and the nutritional risk score (*Screening Tool for Risk on Nutritional status and Growth score*) [18] will be calculated, and the *Risk-Adjustment in Congenital Heart Surgery* classification [19] for patients of cardiac surgery will be recorded. In addition, comorbidities, such as the presence of a congenital disease or syndrome, gestational age at birth, presence or history of cancer, diabetes mellitus, kidney disease, liver disease, chronic heart disease, home ventilatory support, and sepsis upon admission, will be noted. In addition, for all patients, baseline results of routine clinical chemistry will be recorded.

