#### Secondary End Points

Secondary end points will comprise outcomes regarding the safety, feasibility, and efficacy of the intervention. The primary safety outcome is defined as the difference in the incidence of severe and resistant hypoglycemic events and severe gastrointestinal complications between the groups. For definitions of severe and resistant hypoglycemia and severe gastrointestinal complications, see the *Discontinuation of the Study Intervention* section*.*

The secondary safety outcomes comprise the following:

Overall blood glucose control (hypoglycemic incidents and hyperglycemic incidents)Complications of nutritional supportHyperlactatemia during the feeding interval

As patients with a feeding and fasting cycle in the *intermittent* group may be considered at increased risk for hypoglycemia during the fasting interval, we will also report hypoglycemic incidents (glucose <2.2 mmol/L) during the time window of the randomized intervention for both groups as the number of nights with at least one episode of hypoglycemia divided by the total number of days of the intervention. As patients in the *intermittent* group may be considered at increased risk for hyperglycemia during the condensed feeding period, we will report the hyperglycemic incidents (glucose >10 mmol/L) during the time window of the randomized intervention for both groups as the number of days with at least one episode of hyperglycemia divided by the total days of the intervention.

Possible complications of nutritional support are shown in Textbox 1.

Hyperlactatemia is defined as an increase in arterial lactate levels above 2 mmol/L during the feeding interval.

Other secondary outcomes will be feeding intolerance and metabolic (eg, course of ketones, lactate, and free fatty acids) and endocrine responses (eg, insulin and glucagon). Enteral feeding intolerance is defined according to the definition by Eveleens et al [34] (Multimedia Appendix 1). Furthermore, we will evaluate any observed effects of the intermittent feeding strategy compared with continuous nutrition on nutritional intake, circadian rhythm, and clinically relevant outcome measures.

The effects on nutritional intake and circadian rhythm that will be investigated are presented in Textbox 2.

Clinically relevant outcome measures will be collected until 30 days after admission and are presented in Textbox 3.

Possible complications of nutritional support.

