### Statistical Analysis

#### General Rules

A CONSORT (Consolidated Standards of Reporting Trials) flow diagram will be reported [39]. All analyses will be primarily performed according to an intention-to-treat analysis. To perform additional per-protocol analysis, we anticipated that up to 30% of the patients will not be able to receive artificial nutrition during their admission to the PICU.

Categorical variables will be summarized as counts and frequencies and analyzed using the chi-square test or Fisher exact test. Continuous variables will be summarized using either mean and SD or median and IQR, depending on the distribution of the variables.

All analyses will be performed primarily for the complete group. In secondary analyses, analyses can be stratified according to different age groups (neonates, infants, and children). Adjustment for baseline risk factors, including the diagnostic group, age group, severity of illness, and severity of nutritional risk, will only be used for secondary analyses. Multiple imputation will only be used in secondary analyses to deal with missing data for confounders. For all end points, differences will be considered statistically significant when the 2-sided *P* value is <.05 or when the 1-sided *P* value is <.025 in the case of noninferiority tests, without correcting for multiple testing.

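### The yes/no renal replacement therapy outcome counts children who entered the trial because they were already on that therapy

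*Protocol article*

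**What the plan says.** In the protocol article, the list of clinically relevant outcome measures has an acute kidney failure item with two parts. The first is renal replacement therapy (RRT): "Patients in need of renal replacement therapy (RRT) during PICU stay and the duration of RRT (for patients requiring RRT"). The second is "Patients with acute kidney injury according to the" pediatric RIFLE criteria.

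The Inclusion Criteria section gives three ways of being considered critically ill. One is "Continuous renal replacement therapy on account of acute renal failure". The Exclusion Criteria section does not exclude children with existing acute RRT or kidney injury.

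In the same outcome list, infections count only if newly acquired, and the liver item reads "Patients with newly acquired liver failure according to the" cited criteria.

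On timing, for unplanned admissions "informed consent will be obtained within 24 hours after becoming eligible for the study". The Secondary End Points section states that "Clinically relevant outcome measures will be collected until 30 days after admission", so the window is tied to admission and not to randomization.

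On baseline data, the comorbidities recorded at study entry include "presence or history of cancer, diabetes mellitus, kidney disease, liver disease, chronic heart disease", and routine clinical chemistry is recorded too. RRT status at entry is not listed. The General Rules section plans, for secondary analyses only, "Adjustment for baseline risk factors, including the diagnostic group, age group, severity of illness, and severity of nutritional risk". Kidney status at entry is not named among these factors.

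**The concern.** An outcome meant to compare two feeding schedules should record events that the schedule could cause or prevent. A child admitted to the trial because of continuous RRT already satisfies the yes/no RRT outcome, whatever arm is assigned.

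Such children add the same expected background to both arms. This pulls the risk ratio toward 1, in the direction of hiding a benefit or a harm. A chance difference between arms in the number who entered on RRT also goes straight into the comparison. Randomization is stratified by age group only, so nothing in the design balances RRT at entry beyond chance.

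The two neighbouring items show that the authors had the needed limit in mind. Of the three organ or infection items, the kidney item is the one whose condition is also an entry criterion, and it is the one without the limit.

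**Working it through.** The article states no rate, effect size or power for the kidney outcome, so there is no figure to reproduce. The check is textual first, then an illustration.

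**Do the two definitions overlap?**

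1. Continuous RRT for acute renal failure is enough to be classed as critically ill (Inclusion Criteria).
2. No exclusion removes such a child (Exclusion Criteria).
3. The randomization tool allocates eligible patients. A child eligible by this route is therefore on RRT before allocation, and in unplanned admissions consent may follow eligibility by up to 24 hours.
4. The outcome is any need for RRT in the PICU stay, without a requirement that it start after allocation.

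The child in step 1 therefore meets the outcome in step 4 by definition.

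**How much could it matter?** Inputs from the article: 70 children per arm, two-sided 5% level. Assumed, because the article gives neither: the share *b* on RRT at entry (equal in both arms) and the risk of new RRT in the remaining children.

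Counted risk in an arm = *b* + (1 − *b*) × new-event risk.

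With assumed new-event risks of 10% and 5% (true risk ratio 0.50, true difference 5 points):

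| *b* | Counted risks | Risk ratio | Difference (points) |
|---|---|---|---|
| 0 | 10.0% vs 5.0% | 0.50 | 5.0 |
| 5% | 14.5% vs 9.75% | 0.67 | 4.75 |
| 10% | 19.0% vs 14.5% | 0.76 | 4.5 |
| 20% | 28.0% vs 24.0% | 0.86 | 4.0 |

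For example, at *b* = 10%: (0.10 + 0.90 × 0.05) / (0.10 + 0.90 × 0.10) = 0.145 / 0.190 = 0.76. Read as a harm, the same case turns a true ratio of 2.0 into 0.190 / 0.145 = 1.31.

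Power by the normal approximation, with d the difference in risks p₁ and p₂, p̄ their mean, and n the children per arm: Φ{[|d|√n − 1.96√(2p̄(1 − p̄))] / √(p₁(1 − p₁) + p₂(1 − p₂))}. A more favourable pair of assumed risks, 20% and 10%, gives:

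| *b* | Counted risk ratio | Power, all counted (n = 70) | Power, at-risk children only (n = 70(1 − *b*)) |
|---|---|---|---|
| 0 | 0.50 | 38% | 38% |
| 5% | 0.60 | 30% | 36% |
| 10% | 0.68 | 24% | 35% |
| 20% | 0.78 | 17% | 32% |
| 30% | 0.84 | 13% | 28% |

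**Noise from chance imbalance.** The SD of the between-arm difference in the share on RRT at entry is √(2*b*(1 − *b*)/70). At *b* = 10% this is √(0.18/70) = 0.051, about 5 percentage points. That is as large as the assumed 10% versus 5% effect. At *b* = 2% it is 2.4 points.

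**The case against.** **The analysis plan for secondary outcomes is to be published separately, and could restrict the at-risk set.** It could, and the article does not forbid it. But the outcome definition is set in this article, and as worded it includes the entry cases.

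**The size is built on assumptions and on the ratio scale.** This stands. The article gives no prevalence or event rate and plans chi-square or Fisher tests without naming a risk ratio. On the absolute scale the loss is small: 5.0 points becomes 4.5 at *b* = 10%. Power is low under either definition: about 20% for 10% versus 5% even with nobody on RRT at entry.

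**Three stronger readings are tempting and are not supported:**

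- *That the trial would report a biased or false renal effect of overnight fasting.* Allocation is random, so children on RRT at entry are balanced in expectation. What remains is dilution and noise. The Strengths and Limitations section already says that the sample is too small for conclusions on clinical outcomes.
- *That the kidney injury count demonstrably has the same fault.* The PICU-stay window is attached to the RRT part only. The kidney injury part states no window and relies on an external criterion whose handling of baseline function cannot be checked here. Counting injury present at entry is a natural reading, but it rests on silence.
- *That RRT duration is invalid because it includes children on RRT at entry.* The article also scores the durations of ventilation and of hemodynamic support, which are entry criteria too. Feeding could affect how long RRT is needed, so these children belong in the duration measure. The only open matter is the starting point of the clock: the article does not fix it at randomization, so days before allocation could be included.

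**Conclusion.** The point holds for the yes/no RRT component. Two definitions in the article overlap, so children on continuous RRT before allocation are counted as events in either arm, while the infection and liver failure items are protected by a newly acquired limit.

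The effect is dilution of the relative comparison and added noise in one secondary outcome. Its size cannot be stated. The risk ratios of 0.67 to 0.86 (true value 0.50) hold only if new-event risks are 10% and 5% and if 5% to 20% of children enter on RRT. If few children enter by the renal route, the effect is small.

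The correction is still worthwhile. The result will be reported, and the article foresees a larger trial on clinical outcomes that may draw on it.

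**What to change.** Before the allocation is unblinded for analysis, restate the item as follows:

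- **RRT, yes/no:** first RRT started after randomization, among children not on RRT at randomization.
- **RRT at entry:** number and percentage by arm, reported separately.
- **RRT duration:** counted from randomization, with children on RRT at entry kept in the measure.
- **Kidney injury:** new or worsened pediatric RIFLE stage compared with entry, where the entry chemistry allows a baseline stage. State how many children have no baseline stage.

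The cost is a slightly smaller denominator and fewer counted events for the yes/no outcome. Kidney status at entry must also be derived. The article lists kidney disease as a comorbidity and routine chemistry at baseline, but not RRT status or an injury stage, so these would have to come from the clinical record. With 132 of 140 children enrolled by May 2022, most of this is retrospective work. It needs no new measurement in children whose record holds the data, and people blinded to allocation can do it.

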#### Other Outcomes

Further metabolomic, endocrine, and inflammatory measurements on stored samples in the context of mechanistic analyses are planned. Moreover, these samples may be used for pharmacokinetics, pharmacodynamics, and autophagy analyses. In addition, we will evaluate parental stress (*Parental Stress Score*–PICU) [37] and the overall workload among (PICU) nurses (National Aeronautics and Space Administration Task Load Index) [38]. The detailed protocols and methods for the statistical analyses for these outcomes will be reported separately. Finally, a follow-up study after enrollment in the ContInNuPIC (concerning, eg, neurocognitive and physical function) will be planned as well; however, the details are beyond the scope of this study protocol.

### Trial Organization

The sponsor (Erasmus MC, Rotterdam, The Netherlands) provides direct access to the eCRF, the source data, and the trial master file for monitoring and regulatory inspection. The sponsor has appointed 1 monitor. Monitoring will be performed and reported according to the sponsor’s standard operating procedures. The clinical research team guarantees a daily follow-up of patient screening and inclusion, availability of requested clinical data in the clinical patient files, and protocol compliance. Noncompliance to the protocol and other questions or problems will be discussed with the principal investigator and reported to the study monitor. Regular meetings will be organized between the principal investigator and clinical research team to discuss the daily progression of the ContInNuPIC trial. Serious adverse events occurring during the intervention will be directly reported to the sponsor and the accredited ethical commission (CCMO) and registered in the database.

### Statistical Analysis

#### General Rules

A CONSORT (Consolidated Standards of Reporting Trials) flow diagram will be reported [39]. All analyses will be primarily performed according to an intention-to-treat analysis. To perform additional per-protocol analysis, we anticipated that up to 30% of the patients will not be able to receive artificial nutrition during their admission to the PICU.

Categorical variables will be summarized as counts and frequencies and analyzed using the chi-square test or Fisher exact test. Continuous variables will be summarized using either mean and SD or median and IQR, depending on the distribution of the variables.

All analyses will be performed primarily for the complete group. In secondary analyses, analyses can be stratified according to different age groups (neonates, infants, and children). Adjustment for baseline risk factors, including the diagnostic group, age group, severity of illness, and severity of nutritional risk, will only be used for secondary analyses. Multiple imputation will only be used in secondary analyses to deal with missing data for confounders. For all end points, differences will be considered statistically significant when the 2-sided *P* value is <.05 or when the 1-sided *P* value is <.025 in the case of noninferiority tests, without correcting for multiple testing.

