#### PN Support

During the first week, only EN without supplemental PN will be provided to conform with current guidelines [5,20]. Beyond day 7, if EN is insufficient (<80% of the target intake), parenteral macronutrients will be additionally provided through PN until EN reaches >80% of the target intake. If standard PN formulas are not suitable or are contraindicated for the patient, a tailor-made PN formula can be ordered by the dietician. To reduce the risk of refeeding syndrome on the first day of PN, half the target amount of PN will be provided [24].

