### Intervention Group: Intermittent Nutrition

For patients randomized to the *intermittent* nutrition group (intervention group), all nutritional support will be provided during the day and withheld during the overnight feeding interruption period. The overnight feeding interruption period will be designed in an age-dependent manner. The feeding interruption period will be from 2 AM to 10 AM in neonates (≤44 weeks PMA), from 12 AM until 10 AM in infants (<1 year), and from 10 PM to 10 AM in children (≥1 year), as shown in Figure 2. The daily planned nutritional intake will be provided during the condensed feeding period over the day. The starting time of nutritional intake is set to 10 AM to facilitate procedures that require fasting to be performed in the morning. PN (beyond day 7, if necessary) will be provided during the daily age-dependent feeding periods and tapered over 1 hour during the starting and stopping of PN to reduce the risk of swift metabolic shifts (Figure 2) [25,26].

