### Outcome Measures

#### Primary End Points

The primary outcome of this study will be the feasibility of a daily feeding and fasting cycle (*intermittent feeding* strategy) compared with a continuous 24 hours per day feeding strategy in critically ill children. The primary outcome is defined as the difference in ketosis (3-β-hydroxybutyrate levels) between the groups under the condition of noninferiority regarding caloric intake. The amount of nutritional intake is defined as the daily caloric intake as a percentage of the estimated REE based on the body weight–based or body weight and length–based Schofield equation.

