#### Primary Outcomes

To assess a significant difference in ketosis between the 2 arms, a 2-tailed *t* test will be performed on the patient means of the highest ketone levels in each fasting period (or similar time point in the control group). A linear mixed model will be used to assess the noninferiority of caloric intake (repeatedly measured over time) in the intervention group, with a noninferiority margin of 33%.

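### The caloric noninferiority condition is judged primarily by intention to treat, with no stated role for the per-protocol set, although up to 30% of children may carry little or no treatment contrast

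*Protocol article*

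**What the plan says.** In the protocol article, Primary End Points makes the ketosis comparison conditional on noninferior caloric intake and defines the measure: "The amount of nutritional intake is defined as the daily caloric intake as a percentage of the estimated REE". Calories from parenteral nutrition (PN) are not excluded.

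General Rules sets the analysis population: "All analyses will be primarily performed according to an intention-to-treat analysis". It continues: "To perform additional per-protocol analysis, we anticipated that up to 30% of the patients will not be able to receive artificial nutrition". Noninferiority is concluded "when the 1-sided *P* value is <.025 in the case of noninferiority tests, without correcting for multiple testing". Nothing says that the per-protocol result must agree before noninferiority is declared.

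Primary Outcomes, under Statistical Analysis, specifies a linear mixed model on repeated intake, "in the intervention group, with a noninferiority margin of 33" percent, without naming the scale. Sample Size Calculation instead describes a reduction of more than 33% in cumulative intake corrected for length of stay, which reads most naturally as relative. It also says that the sample was raised by 30% for the per-protocol analysis.

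PN Support provides that beyond day 7, if enteral nutrition (EN) is below 80% of target, "parenteral macronutrients will be additionally provided through PN until EN reaches >80% of the target intake". This applies in both arms. In the intervention arm, "PN (beyond day 7, if necessary) will be provided during the daily age-dependent feeding periods".

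**The concern.** The arms differ in when artificial nutrition runs. A child who never receives it has little or no exposure to that difference, so including such children tends to shrink the observed contrast. In a superiority test this costs power. In a noninferiority test it can produce the favourable answer.

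The protocol foresees the situation and has enlarged the sample for an analysis without these children, but leaves that analysis outside the decision rule. At stake is the feasibility claim that the daily calories can be delivered in a shortened window. The condition could be met partly because some of the sample was never fed under either schedule.

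**Working it through.** **1. The plan's own figures.** Ketone inputs (Sample Size Calculation): difference 0.10, SD 0.16 mmol/L, two-sided 0.05, 90% power.

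n per arm = 2(1.960 + 1.282)² × 0.16² / 0.10² = 53.8, so 54 per arm and 108 in all. 108 × 1.30 = 140.4, which matches 140. If 30% are unfed, 140 × 0.70 = 98 remain, or 49 per arm.

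The caloric power statement cannot be reproduced because no SD is given. Read as 33 points of resting energy expenditure (REE), no true difference, 70 per arm, 80% power and one-sided 0.20 (the stated 80% certainty), it implies an SD of at most 33 / [√(2/70) × (0.842 + 0.842)] = 116 points. At the one-sided 0.025 used in the analysis, the implied SD is 70.

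**2. Margin read as 33 points of REE.** Let the true deficit in fed children be 33 points, and let a fraction f in each arm show no arm difference. The intention-to-treat difference is 33(1 − f). At f = 0.30 it is 23.1, and the fed deficit that would sit on the margin is 33/0.70 = 47.1 points.

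P(declare noninferiority) = Φ([33 − 33(1 − f)]/SE − 1.96), with SE = SD × √(2/70).

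Example, f = 0.30 and SD 30: SE = 5.07; 9.9/5.07 − 1.96 = −0.01; Φ = 0.50.

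| f | SD 30 | SD 40 | SD 50 | SD 60 | SD 70 |
|---|---|---|---|---|---|
| 0.10 | 0.10 | 0.07 | 0.06 | 0.05 | 0.05 |
| 0.20 | 0.26 | 0.16 | 0.12 | 0.10 | 0.08 |
| 0.30 | 0.50 | 0.31 | 0.22 | 0.16 | 0.13 |

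The SDs are assumptions. At SD 116 and f = 0.30 the result is about 0.07. The formula applies one SD to the whole sample. A simulation at f = 0.30 with unfed children scored exactly zero, fed control mean 60-100% of REE and fed SD 20-50 gave 0.17-0.58; at fed SD 30 it gave 0.24-0.43.

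**3. Margin read as a relative 33%.** Assume a fed control mean of 60% of REE and fed SD 30, so the fed intervention mean is 0.67 × 60 = 40.2. Unfed children (30%) have the same mean intake o in both arms. The arm means are 0.7 × 60 + 0.3o and 0.7 × 40.2 + 0.3o. False noninferiority is by simulation.

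| o (% REE, assumed) | Control | Intervention | Relative reduction | False noninferiority |
|---|---|---|---|---|
| 0 | 42.0 | 28.1 | 33.0% | 0.024 |
| 20 | 48.0 | 34.1 | 28.9% | 0.07 |
| 40 | 54.0 | 40.1 | 25.7% | 0.18 |
| 60 | 60.0 | 46.1 | 23.1% | 0.35 |

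Scored as zero, unfed children scale both means by 0.7 and leave the ratio unchanged, so there is no dilution.

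**4. PN after day 7.** Take the additive margin, SD 50 (assumed), everyone fed, and a share w of patient-days beyond day 7 on which PN closes a fraction g of the gap. The difference is 33(1 − wg). For w from 0.10 to 0.30, g = 1 gives 29.7 to 23.1 points and false noninferiority of 0.06 to 0.22. With g = 0.5 it is about 31.3 to 28.1 points and 0.04 to 0.09. The protocol gives neither w nor g.

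**The case against.** Several points on the other side stand.

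- **Scale.** The sample size text points towards a relative reduction. On that scale the bias is nil when unfed children score zero, and otherwise depends on an assumed oral intake.
- **Inputs.** 30% is the protocol's upper limit. In a model of daily intake, children who soon move to oral feeding or discharge contribute few days, so 30% of patients need not be 30% of the weight.
- **The conservative set.** A reader might infer that intention to treat is always the lenient set here and per-protocol the strict one. The document does not support that. Inability to be fed might itself follow from the condensed feeding window. Excluding those children would then remove failures of the intervention, which intention to treat retains.
- **PN.** A reader might also infer that the PN rule makes total calories converge by design. It does not go that far. PN belongs to both allocated strategies, starts only after day 7 and only when EN is insufficient, and is limited to the feeding window in the intervention arm. A per-protocol set would not remove its effect. The secondary endpoints already report first-week attainment of 67% and 100% of predicted REE and the need for PN beyond day 7, though not the same mean contrast.

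It can also be said that the role of the per-protocol set belongs in an analysis plan that is not shown. This carries less weight. The article fixes intention to treat as primary, gives the primary noninferiority model, and defers only the plan for secondary outcomes to a separate publication.

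**Conclusion.** The point holds in a limited form. A condition that gates the primary conclusion is judged primarily on a set in which the protocol itself expects up to 30% of children to receive no artificial nutrition. The per-protocol analysis exists and the sample was enlarged for it; the defect is that it has no stated role in the decision.

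The size is uncertain. At a true margin-sized deficit in fed children, false noninferiority runs from nominal (relative margin, unfed scored zero), through 0.07-0.35 (relative margin, assumed equal oral intake of 20-60% of REE), to about 0.13-0.50 (additive margin, full 30% unfed with equal weight, assumed SD 70 to 30). The upper figures show what the wording permits; they are not an expected error rate. PN after day 7 is a secondary matter of interpretation, relevant to children with longer stays.

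**What to change.** State in the analysis plan:

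1. Noninferiority of caloric intake is declared only if the margin is met in both the intention-to-treat set and a per-protocol (artificially fed) set, the latter defined identically in both arms.
2. Whether the margin is 33 points of REE or a relative 33%, and how children without artificial nutrition, and any oral calories, are scored.
3. The unfed proportion is reported by arm. Intention to treat stays co-required, because being unfed may depend on allocation.
4. As a supporting sensitivity analysis, the same contrast for days 1-7, when only EN is given, since later PN may mask an EN shortfall.

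This changes wording and adds one analysis; it needs no new data. The price is a lower chance of declaring noninferiority. With 49 per arm, 80% power at one-sided 0.025 on the additive scale and no true difference requires an SD of at most 33 / [√(2/49) × (1.960 + 0.842)] = 58 points, against 70 points with 70 per arm.
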